### Biosensor analysis

Biosensors data will be interpreted blinded to CR-P data scored by physiologists according to AASM guidelines to evaluate potential for apnoea detection and interrogation of RR and pattern using RIP bands as ground truth. TcCO_2_ data provide an indicator of hypoventilation.

For neonatal patients, biosensor data will be paired with oximetry data and viewed alongside SpO_2_ trace, recorded RR observation and ventilator measured parameters when available.

For patients with epilepsy, biosensor data will be interpreted in the context of VT, EEG evidence of epileptic seizures and video recording for breathing effort in the peri-ictal period.

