**Trial registration number:**

NCT06292299 pre-results stage.

STRENGTHS AND LIMITATIONS OF THIS STUDYThis study involves data collection from paediatric patients wearing a novel biosensor in a tertiary children’s hospital, with a broad eligibility criteria strengthening external validity.The biosensor data can be paired with standard clinical monitoring data to provide a comprehensive ground truth for data interpretation.Children recruited to this study are at risk of apnoea, sudden death and respiratory failure, a population that may benefit from wearable technology, which can identify changes in respiratory metrics.Movement artefact has the potential to impact the visualisation of the respiratory waveform; however, actigraphy as a metric can have value in monitoring the clinical condition.

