**Figure 2 F2:**
[figure not shown]
On-site workflow for observational study. Group 1 includes children attending for cardiorespiratory polygraphy; group 2 includes neonates staying in the neonatal unit or postnatal ward and group 3 includes children attending the epilepsy monitoring unit for video telemetry. Green boxes represent ethics forms. CR-P, cardiorespiratory polygraphy; DCM, data capture mobile; PEWS, Paediatric Early Warning Score; PIS, participant information sheet; VT, video telemetry.

**Table 1 T1:** Data sources

Patient group	PneumoWave sensors worn	Standard clinical monitoring data	Outcome of interest
Cardiorespiratory sleep study patients	Chest and abdominal sensor	Thoracic and abdominal RIP channels, RIP sum, Oximetry (SpO_2_ and HR), ECG, body position, movement and nasal pressure flow (all children), video, audio and TcCO_2_ (some children)	Tolerability of PneumoWave device Feasibility of data collection from PneumoWave device RR Apnoeas and hypopnoeas (obstructive, central, mixed)
Neonatal patients	Chest sensor	Oximetry (SpO_2_ and HR)	Tolerability of PneumoWave device Feasibility of data collection from PneumoWave device RR Central apnoeas/periodic breathing
Epilepsy patients attending for video telemetry	Chest sensor	Oximetry (SpO_2_ and HR) Video EEG Feedback forms completed by parents and children >5 years of age	Tolerability of PneumoWave device Feasibility of data collection from PneumoWave device RR Central apnoeas in peri-ictal period Respiratory pattern in peri-ictal period Parent/patient feedback on biosensor acceptability

EEG, electroencephalogram; HR, heart rate; RIP, respiratory inductance plethysmography; RR, respiratory rate; SpO_2_, peripheral oxygen saturation; TcCO_2_, transcutaneous carbon dioxide.

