### Statistical analysis

Data was stored in Microsoft Excel and analysed using PRISM 10 (San Diego, California, USA). Demographic data, feedback forms and descriptive data will be reported using means and SD for continuous data. Absolute number and percentages will be reported for categorical data. Any statistical software can be used. For reference events (eg, apnoeas) or respiratory metrics (eg, RR), Root Mean Square Deviation to quantify the accuracy of manually annotated biosensor data (and developmental algorithm results) compared with standard care. A target accuracy of ±2 bpm/% of RR will be predefined as clinically acceptable error margin. Bland-Altman analysis will additionally be performed to visualise the bias between measurements. For respiratory event identification (eg, central apnoea), a confusion matrix stating the true positive (TP), false positive (FP) and false negative (FN) values of biosensor data (and developmental algorithm detection) of a specific respiratory event will be generated. Receiver operating characteristic curve analysis will be undertaken to evaluate the predictive performance of algorithms for evaluating central apnoeas in CR-P patients.

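### Biosensor traces are read blind only in the polygraphy group, yet accuracy statistics for manual annotations are not limited to that group

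*Protocol article*

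**What the plan says.** All references are to the protocol article.

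**Reading conditions (Biosensor analysis).** Each group has its own sentence.
- Polygraphy: "Biosensors data will be interpreted blinded to CR-P data scored by physiologists according to AASM guidelines", with the inductance bands as ground truth.
- Neonates: "For neonatal patients, biosensor data will be paired with oximetry data and viewed alongside" the SpO2 trace, and also "recorded RR observation and ventilator measured parameters when available".
- Epilepsy: "biosensor data will be interpreted in the context of VT, EEG evidence of epileptic seizures and video recording", the video being there to judge breathing effort around seizures.

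Blinding is not stated for the second or third group anywhere in the article.

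**Statistics (Statistical analysis).** Root mean square deviation (RMSD) is to quantify the "accuracy of manually annotated biosensor data (and developmental algorithm results) compared with standard care". Bland-Altman analysis is added for bias, and a matrix of true positives, false positives and false negatives for respiratory events. None of these names a patient group. The ROC analysis does: it is for central apnoea algorithms in polygraphy patients.

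**Outcomes and reference.** Table 1 lists respiratory rate and central apnoea as outcomes of interest in all three groups. The neonatal entry includes "RR Central apnoeas/periodic breathing", and its only listed monitoring is oximetry. Secondary outcome measures makes standard monitoring the ground truth; its examples include rate counts by the clinical team and ventilator rate and tidal volume. The strengths box says that pairing serves "to provide a comprehensive ground truth for data interpretation".

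**The concern.** An accuracy statistic assumes that the test reading was made without knowledge of the reference. If the annotator can see a desaturation, a charted rate, a ventilator rate or a video of the chest while marking the trace, unclear segments will tend to be resolved towards what is on screen. True positives rise, false positives fall and RMSD shrinks, for reasons that have nothing to do with the sensor. Unclear segments are to be expected, because the article itself warns of movement artefact and places no restriction on normal neonatal activity.

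The authors evidently recognised the issue, since they blinded the polygraphy reading. What is at stake is whether manual accuracy figures from the other two groups can be set beside the polygraphy figures, or carried into the later studies that this one is meant to inform.

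A second, smaller issue concerns neonatal apnoea. A confusion matrix needs a reference that can say whether a central apnoea occurred. For non-ventilated babies the listed sources are oximetry, the plethysmographic rate on postnatal wards, and rate observations. None of these records respiratory effort or airflow.

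**Working it through.** **1. Patients concerned.** Sample size gives 75 per group and 225 in total: 3 × 75 = 225, which reproduces. The two groups without stated blinding hold 2 × 75 = 150, and 150/225 = 66.7%. This is an upper bound, because the article does not say how many of these patients would contribute manually annotated accuracy data.

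**2. Reading condition against statistic, by group.**

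| Group | Reading condition | RMSD, Bland-Altman, event matrix | ROC |
|---|---|---|---|
| Polygraphy | Blind to scored study | Not excluded | Yes |
| Neonates | Alongside SpO2, recorded rate, ventilator data | Not excluded | No |
| Epilepsy | In context of telemetry, EEG, effort video | Not excluded | No |

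The conflict lies in the third column of the lower two rows: statistics that presuppose independent reading, applied to readings described as sighted.

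**3. Which outputs can be affected.** The accuracy sentence covers manual annotations and algorithm results. A fixed algorithm gives the same output whatever a reader sees, so only the manual part is exposed. The primary outcomes are wear time against monitoring time, removal, and data capture in situ. None depends on how the waveform is read.

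**4. How the bias would act (assumed values, for illustration only).** The document gives no rate at which a sighted reader follows the reference.

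*Events.* Let s be the blinded sensitivity, and f the share of otherwise missed events that the reader marks because the reference is visible. Observed sensitivity = s + f(1 − s).

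| s | f = 0.10 | f = 0.25 | f = 0.50 |
|---|---|---|---|
| 0.60 | 0.64 | 0.70 | 0.80 |
| 0.70 | 0.73 | 0.775 | 0.85 |
| 0.80 | 0.82 | 0.85 | 0.90 |

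Over this range the overstatement runs from 2 points (0.82 − 0.80) to 20 points (0.80 − 0.60).

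*Respiratory rate.* If each reading is pulled a fraction w towards the visible value, observed RMSD = RMSD × (1 − w). Taking the article's target as 2 breaths per minute, the pull needed to meet it is w = 1 − 2/RMSD:
- RMSD 2.5: w = 1 − 2/2.5 = 20%
- RMSD 3: w = 1 − 2/3 = 33%
- RMSD 4: w = 1 − 2/4 = 50%

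**5. Neonatal reference by setting (Data collection from patient groups).** Postnatal wards: SpO2, heart rate and a rate derived from the plethysmography waveform. Special care: continuous oximetry, possibly with rate observations. Intensive care with invasive ventilation: ventilator rate, tidal volume, inspiratory time and pressures. A recorded ventilatory measurement therefore exists for ventilated infants. The listed sources for the others contain no effort or airflow signal.

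**The case against.** The best reply is that the neonatal and epilepsy sentences describe viewing and not measurement. The secondary objective is to view the biosensor waveform beside standard monitoring, the statistical text is generic, Table 1 speaks of outcomes of interest, and the Discussion places validation of neonatal algorithms and larger peri-ictal studies in the future. On that reading no manual accuracy figure is planned outside polygraphy, and annotation order could be left to a fuller document.

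This stands in part. The article nowhere says outright that manual accuracy will be reported for neonates or epilepsy, so the bias is conditional on such figures being produced. But the ground-truth statement names ventilator parameters and clinical rate counts as well as polygraphy, and the one statistic meant for polygraphy alone is labelled so. If viewing is purely descriptive, the statistical section should say so. Nor is this just omitted detail: the article states the reading condition for each group.

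Several stronger readings are tempting but are not supported:
- *All accuracy figures in two groups lack independence.* Automated output is not changed by what a reader sees.
- *Neonatal apnoea has no reference at all.* Ventilated infants have recorded rate and tidal volume.
- *EEG is part of the respiratory reference.* The article gives it as evidence of seizures; only the video is tied to breathing effort.
- *The bias has a known size.* Any figure rests on assumed values.
- *Feasibility itself is compromised.* The primary outcomes do not use these readings.

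**Conclusion.** The point holds in a limited form. Blinded reading is specified for one group of three, while RMSD, Bland-Altman and the event matrix for manually annotated data carry no group limit. Followed as written, the plan would yield manual accuracy figures for neonates and epilepsy that are open to review bias and not comparable with those from polygraphy. Up to 150 of 225 planned patients (67%) are concerned. The direction is towards better apparent agreement; the size is unknown.

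The conclusion rests on two premises: that the unrestricted statistical text means what it says, and that viewing alongside or interpreting in context means the comparator is open during annotation. If either fails, what remains is a need to say so. The effect is on secondary accuracy results only. It is worth correcting because the data are meant to inform later studies and the correction is cheap.

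**What to change.** 1. In Biosensor analysis, state for all three groups that manual annotation of the biosensor trace is completed and locked before SpO2, recorded rate, ventilator, polygraphy or video data are opened. In epilepsy, EEG may be used only to mark the peri-ictal window, and the breathing-effort video is withheld until lock.
2. Keep side-by-side viewing as a separate, later step labelled descriptive. It then still serves the secondary objective.
3. If locking is not practicable outside polygraphy, state in Statistical analysis that no manual-annotation accuracy figures will be reported for neonates or epilepsy.
4. In non-ventilated neonates, report central apnoea and periodic breathing descriptively and not in a confusion matrix.

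**Cost.** Items 1 to 3 change the order of reading and some wording; no extra patients, devices or data are needed. Item 4 means that no apnoea accuracy figure is claimed for non-ventilated neonates.

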### Algorithm under test

Developmental versions of central apnoea algorithm/actigraphy algorithm, RR algorithm.

### Data management

Site-specific data including consent forms, ethics documents and CRFs will be stored securely in the clinical research facility at the Queen Elizabeth University Hospital, Glasgow. An Excel spreadsheet which contains patient identifiable information (eg, Community Health Index number) and participant study number will be stored on an NHS computer, password protected and relevant only to individuals in the study team who are permitted to access clinical information.

Anonymised accelerometer data (using study number as reference) from PneumoWave DCM will be stored on a data storage platform (supplied by Galen Data) complete with Health Insurance Portability and Accountability Act requirements. Additionally, Galen Cloud deployed on Amazon Web Services is Health Information Trust Alliance certified.

### Study monitoring/auditing

An annual progress report will be submitted to the funder. Annual reports will be submitted to the ethics committee and sponsor with the first submitted 1 year after the date that all trial-related approvals are in place. This study will be risk assessed by NHS Greater Glasgow and Clyde Health Board Research and Development department, and the audit of this study will be determined by the results of the risk assessment.

### Early withdrawal

Participants may request to withdraw from the study at any stage for any reason without prejudice. Data up until the point of withdrawal will be kept. Should an individual choose to withdraw from the study, no further data will be collected.

### Study procedure risks and benefits

Anticipated risks with biosensor monitoring are expected to be minimal. This is a minimally invasive intervention with no protocol-specified procedures impacting the standard of care. Biosensor data will be analysed retrospectively in parallel with standard care data collected from CRF. Potential study risks include data breaches. However, all electronic data will be anonymous and stored on secure, password-protected devices or servers, and accessible only by approved study personnel. Numerical study IDs will be used in place of participant name.

There is a risk that wearing the sensor may cause distress, especially if patients are already in an unfamiliar environment, sensory processing disorders, concurrent stresses such as seizures from withdrawing antiepileptic medication during VT. Additionally, there may be a risk of skin irritation from the ECG sticker which could not have been foreseen, particularly for VT patients wearing the sensor for consecutive days. The ECG stickers used in this study are designed to be worn for 1 day continuously and will be changed daily, checking skin for irritation.

This study aims to support the development of a future device which can improve respiratory monitoring and apnoea detection for a diverse range of paediatric and neonatal patients in the future. The absence of immediate benefit for the participant will be outlined during the consent process.

### Safety

The capture of safety events will be solely related to adverse device effects (ADEs) and will only be captured for an event relating to the use or wearing of the device. All ADEs will be assessed for severity and reported to the sponsor team.

All ADEs and serious ADEs will be recorded from the time a participant is enrolled until the participant’s monitoring period ends. Participants who have enrolled but then withdrawn prior to wearing the biosensor for the first time will not have adverse events captured. Only unanticipated effects will be captured as reportable ADEs.

### Patient and public involvement

None.

## Ethics and dissemination

The study will be carried out in accordance with the World Medical Association Declaration of Helsinki (1964) standard reporting. Favourable ethical opinion was granted by the Regional Ethics Committee Leeds (IRAS 314696). Patients will only be allowed to enter the study once they have provided assent/consent where appropriate and parental consent has been obtained. Children aged 6–11 years attending for CR-P or VT were eligible to assent to their involvement in the study if able to understand, retain and weigh up information provided in the participant information sheet (online supplemental material 1). Children aged 12–16 years were eligible to consent if they were felt to be able to understand, retain and weigh up information to make an informed decision (online supplemental material 2). Written consent was required from a parent/guardian of each child (onlinesupplemental materials 3  4). Parents/guardians provided consent for neonatal patients. The Chief Investigator will be responsible for updating the Ethics committee of any new information related to the study. The study is registered at ClinicalTrials.gov. Study findings will be reported clearly and transparently with relevant stakeholders including researchers, practitioners and publicly available databases. Results from this study will be presented at national and international conferences and published in peer-reviewed journals.

## Discussion

This protocol will provide initial insights into the feasibility of collecting respiratory data from a wireless wearable biosensor in different patient groups where respiratory monitoring and apnoea detection is critical yet can be challenging. Data collected will be used to identify ‘biomarkers’ to accurately detect respiratory function. Evaluation of RR, pattern and apnoea detection is conceptually simple; however, in clinical practice, they can be challenging due to patient size, tolerance of standard monitoring equipment and reliance on manual interpretation by the clinical team.^37^

Wearable technology provides opportunity to reduce health inequalities, widening access to respiratory monitoring and diagnostic evaluation of SDB. The wireless nature of the biosensor data transmission overcomes geographical boundaries, such as in rural locations in Scotland and non-specialist centres without access to CR-P. Improving the acceptability of diagnostic equipment for patients with neurodevelopmental disorders who find tolerating standard equipment challenging is fundamental to achieving health equity.^1 38 39^

Wearable technology provides an opportunity to harness information from a simple metric (eg, RR and pattern). Application of machine learning may allow for identifications of early clinical deterioration, providing opportunity for intervention. Automated evaluation of respiratory events could reduce the burden of manual interpretation of CR-P and RR. Additionally, there is potential for a closed loop system where therapeutic intervention could be initiated following identification of a respiratory ‘biomarker’ or trend in respiratory pattern, such as patients requiring non-invasive ventilation to support their breathing.

This feasibility study has multiple strengths; we will evaluate the acceptability of this wearable sensor in a tertiary children’s hospital alongside standard clinical care. We have used a broad eligibility criteria and will include a diverse range of patients, including those with comorbidities and neurodevelopmental disorders, strengthening the external validity of this study. Patients included in this study are at risk of apnoeas, respiratory failure or sudden unexpected death, evaluating feasibility in a population who may benefit from continuous respiratory monitoring with a wearable biosensor. No restrictions were placed on normal activities such as feeding, cares and skin to skin for neonatal patients which may introduce movement artefact, enabling real-world testing. Feedback from patients and parents will be valuable and guide necessary modifications to optimise comfort and acceptability for patients and families.

Limitations exist in this study. First, movement artefact may limit visualisation of respiratory waveform at times; however, this is representative of real-world use and actigraphy as a metric can be useful for tracking clinical condition. Second, issues with data capture may occur; for example, ECG electrodes may be displaced. However, this is not directly related to the device under test (PneumoWave adhesive in the development pipeline).

Innovation within paediatric respiratory monitoring is required as existing devices are poorly tolerated by many children, resulting in high rates of incomplete and inconclusive investigations. Development of user-friendly and cost-effective devices offers additional opportunities to increase the duration and frequency of investigative periods. Wearable devices provide opportunity for longitudinal monitoring for the detection of life-threatening respiratory deterioration in real-time and alerting of carers to improve survivability. Future development of this work will involve conducting randomised clinical investigations of the biosensor to evaluate the potential integration of the biosensor within clinical pathways and collect health economics and outcomes data. Non-inferiority studies will determine the effectiveness of algorithms, for example, respiratory event identification in children attending for SDB evaluation. Larger scale studies monitoring patients with epilepsy at risk of SUDEP such as Dravet’s syndrome will provide additional information around respiratory changes in the peri-ictal period, currently poorly understood due to the difficulties of data capture with existing devices in this patient group. Bespoke neonatal algorithms can be tested and validated against standard clinical monitoring data.
